## Abstract

**Background:**

Injury is a global health concern, and injury-related mortality disproportionately impacts low- and middle-income countries (LMICs). Compelling evidence from observational studies in high-income countries shows that trauma education programs, such as the Rural Trauma Team Development Course (RTTDC), increase clinician knowledge of injury care. There is a dearth of such evidence from controlled clinical trials to demonstrate the effect of the RTTDC on process and patient outcomes in LMICs.

**Objective:**

This multicenter cluster randomized controlled clinical trial aims to examine the impact of the RTTDC on process and patient outcomes associated with motorcycle accident–related injuries in an African low-resource setting.

**Methods:**

This is a 2-arm, parallel, multi-period, cluster randomized, controlled, clinical trial in Uganda, where rural trauma team development training is not routinely conducted. We will recruit regional referral hospitals and include patients with motorcycle accident–related injuries, interns, medical trainees, and road traffic law enforcement professionals. The intervention group (RTTDC) and control group (standard care) will include 3 hospitals each. The primary outcomes will be the interval from the accident to hospital admission and the interval from the referral decision to hospital discharge. The secondary outcomes will be all-cause mortality and morbidity associated with neurological and orthopedic injuries at 90 days after injury. All outcomes will be measured as final values. We will compare baseline characteristics and outcomes at both individual and cluster levels between the intervention and control groups. We will use mixed effects regression models to report any absolute or relative differences along with 95% CIs. We will perform subgroup analyses to evaluate and control confounding due to injury mechanisms and injury severity. We will establish a motorcycle trauma outcome (MOTOR) registry in consultation with community traffic police.

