##### Patient Participants

We will include patients who sustain motorcycle accident–related injuries and present to the study sites within 24 hours following the accident, as defined in a previous study [6]. These will include passengers on motorcycles, motorcycle riders, pedestrians or cyclists hit by motorcycles, and patients experiencing motorcycle-motorcycle collisions, motorcycle-static object collisions, or motorcycle-car collisions.

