#### Methods for Additional Analyses

Subgroup analyses will be performed for (1) varying road user categories (pedestrian, passenger, and motorcyclist); (2) injury mechanisms (motorcycle-motorcycle accident, motorcycle-pedestrian accident, motorcycle-static object accident, and motorcycle-car accident); (3) varying injury severities (mild, moderate, or severe based on the KTS and GCS); and (4) multiplicity of serious injuries (one or multiple). To determine the training-effect heterogeneity across time periods, we will use an extension of Hussey and Hughes fixed effects model [49] for determining whether the intervention effect differs for each training period as summarized in the schematic representation of the study design (Multimedia Appendix 7).

For the ancillary study on provider outcomes, the difference in pretraining and posttraining mean scores will be computed with 95% CIs if the data are normally distributed; otherwise, the difference in median and IQR will be reported. For the qualitative ancillary study on the perceived barriers to injury care, directed content analysis of themes of transcribed data will be collated manually and presented as percentages.

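### The abstract gives subgroup analyses the task of controlling confounding, no adjusted model is fixed for the two primary intervals, and the subgroup lists omit eligible cyclists

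*Protocol article*

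**What the plan says.** The Methods part of the abstract makes two statements in a row. The first is on reporting: "We will use mixed effects regression models to report any absolute or relative differences along with 95% CIs". The second is on confounding: "We will perform subgroup analyses to evaluate and control confounding due to injury mechanisms and injury severity".

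The strata are listed under Methods for Additional Analyses, which does not mention confounding:

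- "varying road user categories (pedestrian, passenger, and motorcyclist" (3 levels)
- "injury mechanisms (motorcycle-motorcycle accident, motorcycle-pedestrian accident, motorcycle-static object accident, and motorcycle-car accident" (4 levels)
- "varying injury severities (mild, moderate, or severe based on the KTS and GCS" (3 levels, or 6 if the two scores are run separately)
- "multiplicity of serious injuries (one or multiple" (2 levels)

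Under Secondary (Patient) Outcomes, the label 'subgroup analyses' is used for something else: mixed models with covariates. The list for an unfavorable TOMS includes road user category and the Kampala Trauma Score (KTS). The list for mortality includes injury mechanism and the Glasgow Coma Scale (GCS). A Mantel-Haenszel step with interaction terms follows the mortality list. Plans for Assessment and Collection of Outcomes adds the baseline expectation score, GCS and KTS as covariates, without tying them to an outcome.

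For the two primary intervals, Primary (Process) Outcomes gives a two-sample t test or a Wilcoxon test and no covariates. The Outcomes section and Study Limitations mention mixed models in general terms.

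The patient eligibility criteria admit "pedestrians or cyclists hit by motorcycles".

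**The concern.** Confounder adjustment and subgroup analysis answer different questions. Adjustment gives one overall arm effect freed from imbalance in case mix. A subgroup analysis asks whether that effect varies with a patient characteristic. The article uses one term for both, so a reader of the abstract cannot tell which is meant for mechanism and severity.

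Case-mix imbalance is a practical risk here. Three hospitals per arm are randomized, Sequence Generation states that no stratification factors are used, and Study Limitations concedes that differences between hospitals could bias the estimates. If the primary intervals are analyzed as their own section says, nothing in that analysis corrects for such an imbalance, and separate stratum results do not yield the single adjusted effect that readers will want.

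The missing cyclist category is a second, smaller problem. Patients who meet the inclusion criteria would have no stratum in two of the four subgroup analyses. Road user category is also a covariate in the TOMS model, so the same coding would carry the gap there.

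**Working it through.** **1. Where confounding control is stated, outcome by outcome**

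| Outcome | Adjusted analysis named | Mechanism | Severity |
|---|---|---|---|
| Unfavorable TOMS | Mixed model with covariates | Road user category only | KTS |
| Mortality | Mixed model with covariates; Mantel-Haenszel | Yes | GCS |
| Two primary intervals | None in their own section; mixed models mentioned generally elsewhere | Only the abstract's subgroup sentence | GCS and KTS as covariates, not tied to an outcome |

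The Mantel-Haenszel step does not fill the last row: in its usual form it pools effects on a binary outcome, and the intervals are continuous. For mechanism and the primary intervals, the abstract's sentence is therefore the only specific statement on confounding.

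**2. What stratifying does and does not do**

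A simulated example (2000 runs, one three-level confounder, true effect -1.00 h) gave:

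- crude difference: -1.24 h
- effect within each of the three strata: -1.00 h on average
- pooled over strata: -1.00 h
- regression with the factor as covariate: -1.00 h

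Stratifying removes confounding by the stratifying factor, and pooling returns one adjusted estimate. Left unpooled, the stratum estimates are less precise. Their standard deviations were 0.163, 0.207 and 0.260 h against 0.114 h pooled, which is 0.163/0.114 = 1.4 to 0.260/0.114 = 2.3 times as large. One factor at a time also leaves mechanism and severity not handled together.

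**3. False positives if every stratum were tested at 5%**

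The article states no subgroup error rate, so there is no figure to reproduce. For independent tests the chance of at least one false positive is 1 - 0.95^k:

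- mechanism and severity, k = 4 + 3 = 7: 1 - 0.95^7 = 30%
- all four factors, k = 3 + 4 + 3 + 2 = 12: 1 - 0.95^12 = 46%

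Strata from different factors share patients, so the tests are correlated. A simulation used 6 hospitals, 720 or 1002 patients, an SD of 1.64 h, assumed stratum shares and 400 runs per scenario (Monte Carlo standard error about 2.5 points). Without clustering it gave 26-34% for 7 levels and 37-42% for 12 levels. With hospital clustering (ICC 0.02-0.05) and a cluster-level test it gave 19-35%. Patient-level tests that ignore clustering gave more, but the overall test was then falsely positive in 27-54% of runs, so much of that excess has another cause.

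One interaction test per factor gives 1 - 0.95^2 = 10% for two factors (simulated 8-13%) and 1 - 0.95^4 = 18.5% for four (simulated 15-22%).

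**4. Eligibility against the category lists**

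Eligible road users are motorcycle riders, motorcycle passengers, pedestrians and cyclists. The subgroup list has the first three. Eligible events include a motorcycle striking a cyclist. The mechanism list has a second motorcycle, a pedestrian, a static object and a car, but no bicycle. A cyclist therefore has no stratum under either factor.

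**The case against.** The strongest reply is that the body of the article shows what the authors mean by the phrase. For TOMS and mortality, their 'subgroup analyses' are covariate-adjusted mixed models, severity scores are named as covariates, and interaction terms are planned. The list of true strata sits under additional analyses and makes no claim about confounding. This stands for the secondary outcomes. It does not reach the primary intervals, whose section names no covariates.

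A reader might infer that subgroup analyses are incapable of controlling confounding. That goes too far: step 2 shows that stratifying, with pooling, does it for the stratifying factor.

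A reader might also infer that the trial will be analyzed by separate tests in each stratum and will often show conflicting results. The documents do not say that within-stratum P values will be interpreted. Nor does the planned effect suggest frequent conflict. A difference of 1.02 h with an SD of 1.64 h is 1.02/1.64 = 0.62 SD. With 1000 independent patients and assumed shares, the smallest road-user stratum (25%, 125 per arm) has 0.62 x sqrt(125/2) = 4.9 standard errors of signal, and a severity stratum of 10% (50 per arm) has 0.62 x sqrt(50/2) = 3.1. Strata would then disagree on significance in about 0.2% of trials for road user and 13% for KTS. Much higher rates need a far smaller effect, about 0.18 SD. Across the simulated scenarios with a 1 h effect, a mix of significant and non-significant strata occurred in 1-89% of runs, and estimates of opposite sign in at most 6%. No single rate of conflict can be claimed.

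It can also be said that interaction tests and exploratory labels belong in an analysis plan. Their absence alone would not be a finding. Giving subgroups the job of confounding control, and listing categories that do not cover the eligible patients, are things that this article itself states.

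**Conclusion.** The point holds as a matter of wording and specification. The abstract merges confounder adjustment with effect-modification subgroups. The consequence falls on the two primary intervals, for which the article fixes only unadjusted two-sample tests and ties no interaction test to the listed subgroups. Separately, the subgroup categories leave eligible cyclists without a stratum under road user and mechanism. How many patients this affects cannot be told from the document.

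The error rates in step 3 apply only if each level were tested at 5%. They rest on assumed stratum shares, a two-sided test and, for the 26-34% and 37-42% ranges, no clustering. They show why one interaction test per factor is preferable; they are not a forecast of what the trial will report.

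**What to change.** - **Abstract, Methods:** remove confounding control from the subgroup sentence. State that it rests on prespecified baseline covariates (injury mechanism, KTS, GCS) in the overall mixed model, and name that model for the two primary intervals.
- **Secondary (Patient) Outcomes:** call the covariate-adjusted models by that name, not subgroup analyses.
- **Methods for Additional Analyses:** limit subgroups to effect modification. Use one arm-by-factor interaction test per listed factor in the model for that outcome, show stratum effects with 95% CIs, and label the results exploratory.
- **Categories:** add 'cyclist' to road user, and 'motorcycle-bicycle' and 'other' to mechanism.

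The cost is wording and a few model terms. Plans for Assessment and Collection of Outcomes already includes road user category and nature of collision among the study variables. The main downside is that interaction tests have low power, so fewer subgroup claims will be possible. One caution: the GCS is determined at admission, after any prehospital effect of the training, so for the accident-to-admission interval the plan should say why adjusting for it is acceptable.

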**Results:**

The trial was approved on August 27, 2019. The actual recruitment of the first patient participant began on September 01, 2019. The last follow-up was on August 27, 2023. Posttrial care, including linkage to clinical, social support, and referral services, is to be completed by November 27, 2023. Data analyses will be performed in Spring 2024, and the results are expected to be published in Autumn 2024.

**Conclusions:**

This trial will unveil how a locally contextualized rural trauma team development program impacts organizational efficiency in a continent challenged with limited infrastructure and human resources. Moreover, this trial will uncover how rural trauma team coordination impacts clinical outcomes, such as mortality and morbidity associated with neurological and orthopedic injuries, which are the key targets for strengthening trauma systems in LMICs where prehospital care is in the early stage. Our results could inform the design, implementation, and scalability of future rural trauma teams and trauma education programs in LMICs.

**Trial Registration:**

Pan African Clinical Trials Registry (PACTR202308851460352); https://pactr.samrc.ac.za/TrialDisplay.aspx?TrialID=25763

**International Registered Report Identifier (IRRID):**

DERR1-10.2196/55297

## Introduction

### Background

Transport-related injuries are a global public health threat and are anticipated to rank fifth in the global burden of disease by 2030 [1]. Evidence suggests that 90% of the transport-related crash mortality burden disproportionately occurs in low- and middle-income countries (LMICs), such as those in Africa [1], despite concerns of underreporting [2]. The main causes of injury-related mortality in Africa are road traffic accidents [3], which have serious economic consequences. According to Ryan-Coker et al [4], despite high poverty levels and minimal access to insurance and social protection schemes in Africa, which imply out of pocket expenditure, road traffic accidents cost US $119-$178 per injury and US $486-$12,845 per hospitalization, resulting in a gross domestic product (GDP) loss of 0.8%-9%.

Uganda is one of the LMICs in Africa with a high road traffic injury burden [5]. Our recent studies showed that most fatal injuries in Uganda result from motorized 2-wheeler and car collisions, contributing to 52.6%-64.7% of orthopedic and traumatic brain injuries [6-8]. Further, the majority (74%) of Uganda’s population lives in rural areas [9], which could partly explain the high injury-related mortality rates. Research has shown that the risk of trauma-related deaths in rural areas increases with remoteness owing to health care disparities, such as large commute distances, scarce resources, delays in referral, and lack of skilled trauma care providers, as well as population-specific and contextual challenges, such as poverty and impassable road networks [10].

Uganda lacks universal access to trauma care and injury surveillance systems owing to limited health care funding. Thus, Uganda has made sluggish progress toward attaining the sustainable development goal (SDG3) for universal health care coverage [11]. As such, in terms of the level of specialty care, the ratio of surgeons to patients is 0.7:25,000 as interns and medical trainees represent the largest proportion of Uganda’s health workforce [12,13].

Research has shown than more than half of the trauma patients in Uganda do not receive first aid prior to hospital arrival [6,7]. Moreover, most of these patients arrive at dedicated trauma centers much later than the recommended limit of 1 hour, and they are transported by either public vehicles, such as motorcycles [8], or police vans, without any focus on key factors, such as changes in blood pressure and oxygen circulation, which could lead to death, during transit [7,14]. These aspects have 3 important implications. First, strengthening the capacity for injury care among lay frontline workers. Second, stabilizing patients at rural regional trauma centers prior to transfer. Third, ensuring closed-loop communication between primary (level 3) and tertiary (level 1) trauma centers to enable safely coordinated referrals and adequate preparation at the receiving hospitals prior to patient transfer.

The key challenge that needs to be addressed in Ugandan rural settings is the lack of a formal prehospital care system as evidenced by emergency evacuation and transfer of trauma patients by untrained police staff [14]. Further, there is an immense need to redress the weak immediate care response after an accident as medical trainees are the first point of contact after an accident as opposed to specialists [12]. We will attempt to fix these challenges at the community level and at level 3 rural trauma centers by creating and providing training capacity for rural trauma networks between traffic police and medical interns or trainees at regional referral hospitals.

### Rationale

Evidence from 2 systematic reviews has shown that trauma education programs have the potential to improve skill acquisition and knowledge retention among health professionals; however, with regard to LMICs, most of these programs have not been locally contextualized and have been largely assessed based on their theoretical merit rather than their clinical impact on patients [15,16]. A recent observational study in Portugal showed that the European trauma course (ETC) improved self-efficacy and organization skills in individual routine practice, but the authors mentioned that future investigations should be conducted to examine the effect of the training on trauma outcomes [17]. This European study and systematic reviews in LMICs have recommended high-caliber epidemiological studies to evaluate the effects of such educational programs on process outcomes, such as organizational efficiency, and on patient outcomes, such as morbidity and mortality [15,16,18].

Except for an ongoing pilot trial comparing a primary trauma course (PTC) to advanced life support (ATLS) and routine care in India [19], trauma education programs in LMICs have mostly been evaluated based on nonrandomized studies, limiting their clinical uptake [15]. Moreover, most programs limit the course participants to qualified hospital-based medical providers [18], although interns, medical and allied health trainees, and road traffic law enforcement professionals are the most readily available frontline workers for managing injured patients in LMICs [14]. Inclusive planning while leveraging services that have no trauma designation, such as police services, is critical for expanding and strengthening complex rural trauma systems to improve injury reporting [2].

Locally contextualized trauma training has been identified as one of the most crucial steps for operationalizing nonfunctional rural trauma networks [10]. However, in a scoping review by Brown et al [18], only 12 out of 34 trauma courses in LMICs had been contextualized to suite low-income settings. Moreover, a cautiously executed integrative literature review on the challenges faced by trauma systems recommended that the next step for future research should be an examination of how trauma training impacts the outcomes of patients in remote environments [10]. This multicenter cluster randomized controlled trial will address this gap by examining the effect of the locally contextualized Rural Trauma Team Development Course (RTTDC) of the American College of Surgeons [20] on process and patient outcome measures in Ugandan trauma centers. The trial will focus on musculoskeletal and neurological injuries, which have been recently identified as the most important targets for strengthening health systems in rural Uganda [8], and it has been developed in accordance with the SPIRIT (Standard Protocol Items: Recommendations for Interventional Trials) guidelines for reporting outcomes in trial protocols [21].

### Objectives

#### Broad Objective

The main objective of this trial is to determine the effect of RTTDC training on the time efficiency of the clinical process and the patient-centered outcomes of motorcycle accident–related injuries.

#### Specific Objectives

The specific objectives are to (1) determine the effect of RTTDC training on the time interval from the accident to hospital admission and the time interval from the referral decision to hospital discharge (primary outcomes) and (2) determine the effect of RTTDC training on the outcomes of neurological and musculoskeletal injuries (secondary outcomes).

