### Null Hypothesis

The null hypothesis of this trial is that RTTDC training has no effect on the time efficiency of the clinical process and the outcomes of orthopedic and neurological injuries.

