#### Strategies to Improve Adherence to the Intervention

The RTTDC is the intervention; thus, participants who do not attend all the modules and complete the posttraining MCQs will be excluded. Adherence to teachings in the RTTDC among care providers during clinical practice, such as the time taken from referral decision to execution and improper closed-loop communication leading to loss to follow-up, will be assessed as process measure outcomes.

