Imaging and blood transfusion services are often freely available at emergence units as government services but may be outsourced from private hospitals at a cost owing to long waiting times or service maintenance for CT scanners and X-ray machines. Finally, in terms of patient disposition, patients with minor injuries requiring surgery under local anesthesia are discharged on the same day. Moreover, patients with major trauma requiring conservative treatment, such as closed fractures, are treated in surgical wards, whereas those who are deeply unconscious or require critical care after major operations are admitted to the ICU until they are fit for care in general surgical wards prior to discharge. Alternatively due to overcrowding, often with higher bed occupancy rates exceeding the predetermined bed capacity, patients with major trauma may be referred to other centers, and the common reasons for referral include further neurosurgical evaluation with magnetic resonance imaging or further evaluation by a neurosurgeon, need for multiple specialty care and rehabilitation, and need for ICU admission elsewhere when local ICU beds are limited.

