### Sample Size

To estimate the sample size, we used the open-source R Shiny application for cluster randomized controlled trials with a parallel design and discrete time decay correlation structures for multiple periods [36] available at [37]. Further, we assumed *t*-distribution due to plans for small sample corrections at the analysis stage in accordance with the report by Rutterford et al [38]. The study was approved for 4 years, but the core research team foresaw it feasible to actively collect data for a period of 3 years considering university semester breaks, public holidays, and unexpected events, such as COVID-19–related interruptions, which led to suspension of the trial for 12 months from March 2020 to March 2021. The 3 years (36 months) would yield 12 study periods given the planned training of cohorts of medical students on a 3-monthly basis in accordance with the average duration of internship deployment by the Ugandan Ministry of Health (1-5 months) and the average duration of surgery clinical rotation for university medical students (2 months).

Fixing the study power at 80% for a parallel cluster randomized trial with different cross-sections, considering a discrete time decay period of every 3 months for a total of 12 periods, and assuming correlations to decay with each period, we explored the minimum number of patient participants (cluster size) required per period using the R Shiny application [36]. Assuming a significance level of .05, a within-period intraclass correlation coefficient (ICC) of 0.02 (lower extreme: 0.01, upper extreme: 0.05), and a cluster autocorrelation coefficient (CAC) (ratio of between-period ICC to within-period ICC) of 0.8; allowing for varying cluster sizes with a coefficient of variation of 0.5; and considering a mean difference of 1.02 hours in prehospital transfer time and a pooled standard deviation of 1.64 hours as continuous outcomes reported in a previous observational study from the United States [39], the upper ICC and base CAC plateaued between 5 and 10 participants (Figure 2).

Considering a maximum of 10 participants per cluster period, an 80% power could be attained (Figure 3) and could be met with a total of 3 clusters per arm (Figure 4). This indicates a total of 6 study centers (clusters) drawn from a pool of 17, which reasonably represents 35.3% of Uganda’s regional referral hospitals.

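### The second primary outcome is defined only for patients with a referral decision, which comes after randomisation and is something the intervention network advises on; the two primaries also have no stated testing order

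*Protocol article*

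**What the plan says.** The Specific Objectives name as primary "the time interval from the accident to hospital admission and the time interval from the referral decision to hospital discharge (primary outcomes"). The Abstract and the Outcomes section list the same pair without ranking them. The Null Hypothesis is one broad statement, that "RTTDC training has no effect on the time efficiency of the clinical process and the outcomes of orthopedic and neurological injuries".

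The Sample Size section gives the only significance level and one set of effect inputs: "Assuming a significance level of .05, a within-period intraclass correlation coefficient (ICC) of 0.02 (lower extreme: 0.01, upper extreme: 0.05"), with "considering a mean difference of 1.02 hours in prehospital transfer time and a pooled standard deviation of 1.64 hours". It has no inputs for the second interval. Under Primary (Process) Outcomes, each interval is compared between arms by a two-sample t test or rank sum test, and one hour is the meaningful difference for both.

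On referral, the section on concomitant care says "patients with major trauma may be referred to other centers", while minor injuries treated under local anaesthesia go home the same day. Eligibility does not require referral. The data collection section lists need for referral and the interval from referral to exit as items to record. The Intervention Description has trained teams coordinating referral and a trained resident available around the clock to advise on it.

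The second interval is described in more than one way. It ends at discharge in the objectives and at exit in the data collection section. The adherence section names as a process measure an interval "such as the time taken from referral decision to execution". Under Secondary (Patient) Outcomes it is a mortality covariate cut at one hour, with no value given for patients who were not referred.

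**The concern.** There are two separate issues.

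**Multiplicity.** With two primaries, one alpha and no rule, a reader cannot tell what result would count as success. If either interval could support a claim of better time efficiency, the chance of a false claim exceeds 5%.

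**Conditioning on a post-randomisation event.** This is the more serious issue, and no alpha adjustment repairs it. Randomisation makes all eligible patients in the two arms comparable in expectation. It does not do so for patients later selected by a decision that the intervention may influence. If trained teams refer more patients, fewer, or different ones, the mean interval among those referred can change even when no patient is handled faster or slower. The trial could then report a gain or a loss in efficiency that is only a change in case mix.

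**Working it through.** **Reproducing the plan's figures.** 10 × 12 × 3 = 360 per arm, so 720 in total. 720 × (1 + 9 × 0.02) = 849.6, stated as 850. 850 × 1.18 = 1003, as stated.

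Power for the sized outcome was approximated with these inputs: difference 1.02 h, SD 1.64 h, 3 clusters per arm, 12 periods of 10 patients, cluster autocorrelation 0.8 and cluster-size CV 0.5 (all from Sample Size). The variance is the generalised least squares variance with correlation ICC × 0.8^lag, taking the CV as extra cluster-period variance. The test is a two-sided noncentral t with 2 × 3 − 2 = 4 df; the protocol does not state sidedness.

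- ICC 0.02: standard error 0.181 h, power 98%.
- ICC 0.05: standard error 0.243 h, power 87%.

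Both agree with the stated target of at least 80%. At alpha .025 the same design gives 93% and 73%, so an even split would fall below 80% at the upper ICC.

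**Family-wise error if each outcome is tested at .05 and either suffices.** For independent tests, 1 − 0.95² = 0.0975. With bivariate normal test statistics:

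| Correlation | Family-wise error |
|---|---|
| 0 | 9.75% |
| 0.3 | 9.5% |
| 0.5 | 9.1% |
| 0.8 | 7.8% |

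These figures assume that each test on its own holds 5%.

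**Power for the second outcome.** The protocol gives no effect size, SD or referred share for it. Assume the same 1.02 h and 1.64 h, and let f be the share referred, so that the cluster-period size is 10 × f. At alpha .05:

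| f | Patients (720 × f) | ICC 0.02 | ICC 0.05 |
|---|---|---|---|
| 10% | 72 | 48% | 44% |
| 20% | 144 | 72% | 62% |
| 30% | 216 | 83% | 71% |
| 50% | 360 | 93% | 80% |

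**Size of the selection effect.** Assume that control hospitals refer the most severe 20%, that severity is standard normal and correlates r = 0.3 to 0.5 with the interval, that the SD is 1.64 h, and that training changes no patient's interval. If intervention hospitals refer the most severe share q, the spurious difference is 1.64 × r × [λ(q) − λ(0.20)]. Here λ(q) is the mean severity of the top share q: λ(0.10) = 1.755, λ(0.20) = 1.400, λ(0.30) = 1.159, λ(0.40) = 0.966.

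| q | r = 0.3 | r = 0.5 |
|---|---|---|
| 10% | +0.17 h | +0.29 h |
| 30% | −0.12 h | −0.20 h |
| 40% | −0.21 h | −0.36 h |

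The largest shift is about a third of the one-hour threshold (0.36 / 1), and its sign depends on whether training raises or lowers the referred share.

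**The case against.** The protocol nowhere says that each outcome is tested at .05 or that success on either would be enough. The single .05 stands in the sample-size section, and the broad null, which also covers patient outcomes, is not a decision rule. A multiplicity rule is commonly left to an analysis plan, and that plan is not shown. A both-required rule would cause no inflation. This stands, so the error rate can be stated only conditionally.

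A reader might infer that most patients have no value for the second outcome. The documents do not support that: they give no referred share, and the case definitions are in Multimedia Appendix 3, which is not shown.

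A reader might also infer that the training is known to change who is referred. That goes too far. The Discussion cites earlier evidence on referral decision time, not on the selection of patients, and several listed reasons for referral (crowding, ICU beds, specialist imaging) are capacity limits that a two-day course need not alter. This also stands. It makes the size of any bias unknown, but it does not restore the protection of randomisation: the subset still forms after allocation, through a decision on which the intervention network advises.

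Finally, an all-patient analysis needs home-discharge times, which the listed variables do not show, and any change now comes after the interim analysis. Both limits are carried into the fix.

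**Conclusion.** The point holds in this form. The second primary outcome is, by its wording, conditional on a referral decision made after randomisation, and the plan compares it between arms as if it were a randomised contrast. That follows from the text. How far the comparison could be biased does not: the 0.12 to 0.36 h range rests on an assumed 20% control referral share, assumed severity correlations, and an SD borrowed from prehospital time.

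The multiplicity issue is secondary and conditional. Family-wise error is at most 9.75% for independent tests, lower under positive correlation, and absent if an unseen plan sets an order or requires both. The trial was sized for accident-to-admission time only, and that calculation reproduces. The second primary has no power basis in the protocol; under borrowed inputs it reaches 80% at ICC 0.02 only if somewhat under 30% or more of patients are referred, and at ICC 0.05 only at about 50%.

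**What to change.** Before the outcome analysis:

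1. Make accident-to-admission time the first or sole primary outcome at two-sided .05. The sample-size basis is unchanged, and the power loss from splitting alpha is avoided.
2. Test the referral interval at .05 only if the first test is significant, or make it secondary. In either case, label it as conditional on referral.
3. Report the number and share of patients referred by arm, with their baseline severity (KTS and GCS).
4. Use one name and definition for the interval in the objectives, the adherence section, the data collection section and the mortality model. State how deaths before exit and patients who were not referred are handled.
5. If home-discharge times were collected, add an all-patient sensitivity analysis of time from admission to exit on referral, with home discharge and death as competing events.

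No new patients are needed, and item 5 applies only if the times exist. The referral interval loses its independent claim if the first test fails. The interim analysis took place on August 28, 2022, with allocation codes due to be revealed to the biostatistician at that point, and last follow-up was on August 27, 2023. The change must therefore be dated and documented as made after the interim analysis.
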